### Patients inclusion

All patients were consecutively included when the interventional neurologist confirmed that they met all the inclusion criteria and would treat them with the proposed strategy (SEMTiC strategy), including the use of all three devices. In cases where successful reperfusion (defined as eTICI 2b-3) was not achieved after three passes with the iNdeep, iNedit, and iNtercept devices [all with European Conformity (CE) market], rescue therapy—defined as the use of any additional strategies or devices—was permitted.

Deferred informed consent was utilized to prevent delays in treatment initiation. Once a patient is considered eligible for the study, the patient or their representative receives the “Patient Information Sheet” and “Informed Consent Form” (ICF). Written consent will be required from the patient or a family member during the study period to authorize the use of patient data. Investigators will explain the study and deliver a copy of the signed ICF. Each consented patient will be assigned a unique identifier, composed of a site number and a sequential patient number, based on the order of inclusion at each site.

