### Primary outcomes

#### The primary efficacy endpoint

The primary efficacy endpoint is the achievement of a successful neurothrombectomy, defined as a revascularization of grade ≥2b-3 with ≤3 passes on the eTICI scale (12). The Core Lab used the eTICI scale to assess the performance of the overall system.

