### Statistical analysis

All data will be analyzed with SPSS 27.0 Software. The mean ± standard deviation (SD) will be used if the data are normally distributed, and the median and interquartile range (IQR) will be used if the data are non-normally distributed.

The proportion of patients with eTICI ≥ 2b will be obtained, and the significance level for non-inferiority will be determined using the *Z* statistic for comparing two proportions with a non-inferiority margin of −0.026.

All values will be estimated using the 95% confidence interval (recommended Wilson's or Agresti methods). The following study populations will be defined for statistical analysis:

Intention to treat (ITT) is defined as all patients included in the study who have been treated with at least one of the study devices. The primary efficacy analysis in relation to non-inferiority will be performed on this population.Population by protocol (PP) is defined as ITT subset with no major deviations from the clinical investigational plan. The primary efficacy analysis in relation to non-inferiority will also be performed with this population.Modified population by protocol (PP) is defined as PP subset excluding patients treated with rescue therapy.

All outcomes will be evaluated across all study populations. The proportion of patients undergoing rescue therapy will also be measured. The impact of rescue therapy on both angiographic and clinical outcomes will be assessed using adjusted logistic regression models. A subgroup analysis will compare the results achieved in cases with the occlusion of the M2 vs. the M1/T carotid segments.

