## Discussion

The primary efficacy endpoint of this study is to evaluate the non-inferiority of the iNedit, iNdeep, and iNtercept thrombectomy system in treating acute ischemic stroke in terms of successful recanalization, compared to existing literature. The key efficacy measure (eTICI ≥2b) is a well-established predictor of functional outcomes after mechanical thrombectomy (8). Literature reports successful recanalization rates ranging from 59 to 88% (14, 15).

For the primary safety outcome, we will analyze 90-day mortality, which has been reported to range from 7.9 to 14% in prior studies (3, 9, 15–17), along with any possible serious adverse event as evaluated by an external safety committee.

The secondary prespecified outcome will include eTICI ≥2c following MT, considering that the current goal is to achieve the highest possible percentage of complete or near-complete recanalization (2c or 3). ARISE II trial reported a rate of 64.8% for eTICI ≥2c (3). Favorable clinical outcomes, as measured by mRS of 0–2 at 90 days, will still be evaluated. In previous trials, ~50% of patients achieved this outcome 90 days post-MT (3, 9, 10, 16, 18).

In analyzing secondary outcomes (secondary efficacy outcome V), particular emphasis will be placed on evaluating the TICI score and the degree of recanalization achieved at each pass with the three devices. In addition, a comparative assessment of outcomes with and without rescue therapy will be conducted to understand its impact on procedural success.

Moreover, given the innovative nature of the devices (secondary efficacy outcome VI), thorough attention will be dedicated to evaluating procedure-related complications, including arterial perforation, dissection (particularly involving the ICA), vasospasm, and embolization in new vascular territories. In particular, the risk of balloon rupture will be considered a specific complication associated with using iNedit catheters. It will be recorded and reported during the trial as a *post-hoc* analysis, even if it is expected to have no clinical relevance.

These complications will be systematically assessed by the local investigators, independently reviewed through imaging analysis by the external core lab, and adjudicated by an independent Clinical Events Committee (CEC) to ensure objective evaluation and accuracy.

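### The planned rescue-therapy model would compare three-pass failures with mostly first-line successes, so its odds ratio cannot be read as the impact of rescue

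*Protocol article*

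**What the plan says.** The Statistical analysis section commits to a regression: "The impact of rescue therapy on both angiographic and clinical outcomes will be assessed using adjusted logistic regression models". It names neither the angiographic outcome nor the covariates. The Discussion gives the purpose: "a comparative assessment of outcomes with and without rescue therapy will be conducted to understand its impact on procedural success".

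Patients inclusion sets the condition for rescue: "In cases where successful reperfusion (defined as eTICI 2b-3) was not achieved after three passes with the iNdeep, iNedit, and iNtercept devices". Rescue is then permitted, not required, and is "defined as the use of any additional strategies or devices". The primary efficacy endpoint is success "defined as a revascularization of grade ≥2b-3 with ≤3 passes on the eTICI scale". On its face, the condition for rescue is the complement of primary success.

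Two further statements matter. The Discussion says that eTICI 2b or better "is a well-established predictor of functional outcomes after mechanical thrombectomy". The modified per-protocol population "is defined as PP subset excluding patients treated with rescue therapy", so rescue status also defines an analysis set.

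**The concern.** A patient becomes eligible for rescue by failing first-line treatment. In a contrast of patients with and without rescue, the rescued group consists of three-pass failures and the other group mainly of three-pass successes. By the protocol's own account, that difference is prognostic. The rescue coefficient would mix any effect of rescue with the consequences of three failed passes.

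Adjusting for age, baseline NIHSS and similar variables does not remove this, because the confounder is the three-pass result, which arises after baseline. Adding that result to the model does not help either: among three-pass successes the probability of rescue is zero (positivity fails), so they carry no information on what rescue does.

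At stake is the interpretation of a secondary result. A published odds ratio below 1, described as the impact of rescue, could be taken as evidence against rescue when it mainly reflects who received it.

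**Working it through.** The plan gives no figure for this analysis, so there is none to reproduce.

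**Inputs from the document.** N = 225 and anticipated success of 82% (Sample size determination); 80% success in ITT at 115 patients (Trial status); the rescue condition and the primary endpoint as quoted above.

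**Assumptions, not in the document.** The mRS 0-2 rates, the share of failures rescued, and the proportion *q* of rescued patients whom rescue reperfuses.

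**1. Composition of the two groups.** Failures: 225 × (1 − 0.82) = 40.5, about 41; or 225 × 0.20 = 45. At 82%, 225 − 41 = 184 succeed.

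| Share of failures rescued (assumed) | Three-pass successes, rescued | Three-pass successes, not rescued |
|---|---|---|
| all | 0/41 | 184/184 (100%) |
| three quarters | 0/30 | 184/195 (94%) |
| half | 0/20 | 184/205 (90%) |

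**2. Clinical outcome, rescue without any effect.** Assume mRS 0-2 of 55% after first-line success and 30% after three failed passes.

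- All failures rescued: OR = (0.30/0.70) / (0.55/0.45) = 0.429/1.222 = 0.351.
- Half rescued: the non-rescued rate is (184 × 0.55 + 21 × 0.30)/205 = 107.5/205 = 0.524, so OR = 0.429 / (107.5/97.5) = 0.389.

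The true effect is an odds ratio of 1 in both cases.

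**3. Clinical outcome, helpful rescue.** Assume mRS 0-2 of 55% if finally reperfused and 25% if not, with half of the failures rescued irrespective of prognosis. The rescued rate is 0.25 + 0.30*q*. The non-rescued rate is 0.90 × 0.55 + 0.10 × 0.25 = 0.52 (odds 1.083). Unrescued failures have odds 0.25/0.75 = 0.333.

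| *q* | Rescued rate (odds) | Whole-cohort OR | OR among failures only |
|---|---|---|---|
| 0.3 | 0.34 (0.515) | 0.48 | 1.55 |
| 0.5 | 0.40 (0.667) | 0.62 | 2.00 |
| 0.7 | 0.46 (0.852) | 0.79 | 2.56 |
| 0.9 | 0.52 (1.083) | 1.00 | 3.25 |

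A simulation with the same rates, one measured baseline covariate in the model and 50% to 90% of failures rescued gave whole-cohort adjusted odds ratios of 0.44–0.48, 0.57–0.62, 0.71–0.79 and 0.91–1.00 for the four values of *q*. Among failures only they were about 1.5, 2.0–2.1, 2.6 and 3.2–3.3. Baseline adjustment leaves the distortion in place.

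**4. Angiographic outcome, if it is the primary endpoint.** If the rescue condition is followed exactly, the rescued column in step 1 contains no successes and no finite maximum-likelihood estimate exists. In a fit with 31 rescued patients, the log odds ratio ran through −9.5, −14.5, −24.5 and −41.0 at 5, 10, 20 and 40 iterations, while its standard error rose from 2.9 to 1.2 × 10⁷. One exception makes the estimate finite but extreme: with 1/30 against 184/195, OR = (1/29)/(184/11) = 0.002.

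**5. Angiographic outcome, if it is final eTICI 2b or better.** The rescued group is then not separated, since its success rate is *q*. The non-rescued group is at 90% to 100% by construction. Even at *q* = 0.9 with half of the failures rescued, the two groups are equal at about 90%. If every failure is rescued, the non-rescued group is at 100% and the model is separated from that side.

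**6. Precision of the restricted analysis.** If all failures are rescued, the 95% half-width for a conversion rate near 50% is 1.96 × √(0.25/41) = 0.153, or 0.146 with 45 patients: about 15 percentage points (normal approximation).

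**The case against.** A reader might infer three stronger conclusions, and the document does not support them.

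- **That the model is certain to be separated, with an odds ratio of zero.** The plan does not name the primary endpoint as the angiographic outcome, and final eTICI is at least as natural a reading of procedural success. Even for the primary endpoint, the Core Lab grades the result, while the decision to rescue must presumably rest on the operator's reading during the procedure. A patient rescued on the operator's grade but scored 2b or better by the Core Lab would be a rescued success, and rescue before the third pass could add others. Separation, or near-separation, is conditional.
- **That the model will report harm.** At *q* = 0.9 the simulated odds ratio is 0.91–1.00, which hides a benefit but does not show harm. The figure of 0.35 is a crude odds ratio from assumed rates.
- **That the plan fixes the whole cohort as the analysis set.** It does not say so, and an analysis plan that is not shown could restrict the comparison. However, the Discussion's contrast of outcomes with and without rescue points to an unrestricted comparison, and no choice of baseline covariates would rescue one.

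Two further objections stand in part. The Discussion already plans to examine TICI at each pass, so some of the remedy is in hand. And rescued versus unrescued failures are still selected by the operator, so restriction reduces the confounding without removing it. For that reason the mRS comparison should be descriptive.

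**Conclusion.** The point holds for a whole-cohort rescue term: it compares first-line failures with mostly first-line successes, and its odds ratio does not estimate the impact of rescue. The direction of the distortion follows from the rescue condition together with the protocol's statement that reperfusion predicts function. Its size rests on assumed rates: about 0.35 to 0.39 when rescue does nothing, and at or below 1 in every scenario in which rescue truly helps. Separation is an additional problem only if the primary endpoint is the outcome, or if final eTICI is the outcome and every failure is rescued.

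This is a secondary analysis. The primary non-inferiority test, the sample size and the primary safety endpoint do not depend on it. It is worth correcting because the plan states an aim, the impact of rescue, that this comparison cannot meet.

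**What to change.** - State that no rescue coefficient from the full cohort will be interpreted as the impact of rescue, and name the angiographic outcome.
- Restrict the analysis to patients below eTICI 2b after three study-device passes. List any patient rescued before the third pass separately.
- Report eTICI before and after rescue within patient, and the conversion rate to 2b or better with its confidence interval (Wilson, one of the methods the plan recommends).
- Report 90-day mRS by rescue status among these failures, labelled descriptive.

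The cost is wording. Rescued patients are already followed to 90 days (Completion of the study) and TICI by pass is already planned (Discussion), so no new data collection appears necessary. The price is a denominator of about 41 to 45 patients, intervals of roughly ±15 percentage points at best for a rate near 50%, residual selection by the operator, and possibly few or no unrescued failures. In that last case only the within-patient result remains. The change concerns analysis and reporting only, not who receives rescue.

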### Trial status

The analysis after 115 patients showed non-inferiority of the SEMTiC strategy using iVascular devices in achieving the primary efficacy endpoint (80% in ITT and 89% in PP populations). These 115 patients had enough statistical power to finish recruitment at that point. However, the increase in the sample size to *N* = 225 was designed to obtain additional real-life clinical data. The study completed recruitment on June 30, 2024.

## Discussion

The primary efficacy endpoint of this study is to evaluate the non-inferiority of the iNedit, iNdeep, and iNtercept thrombectomy system in treating acute ischemic stroke in terms of successful recanalization, compared to existing literature. The key efficacy measure (eTICI ≥2b) is a well-established predictor of functional outcomes after mechanical thrombectomy (8). Literature reports successful recanalization rates ranging from 59 to 88% (14, 15).

For the primary safety outcome, we will analyze 90-day mortality, which has been reported to range from 7.9 to 14% in prior studies (3, 9, 15–17), along with any possible serious adverse event as evaluated by an external safety committee.

The secondary prespecified outcome will include eTICI ≥2c following MT, considering that the current goal is to achieve the highest possible percentage of complete or near-complete recanalization (2c or 3). ARISE II trial reported a rate of 64.8% for eTICI ≥2c (3). Favorable clinical outcomes, as measured by mRS of 0–2 at 90 days, will still be evaluated. In previous trials, ~50% of patients achieved this outcome 90 days post-MT (3, 9, 10, 16, 18).

In analyzing secondary outcomes (secondary efficacy outcome V), particular emphasis will be placed on evaluating the TICI score and the degree of recanalization achieved at each pass with the three devices. In addition, a comparative assessment of outcomes with and without rescue therapy will be conducted to understand its impact on procedural success.

Moreover, given the innovative nature of the devices (secondary efficacy outcome VI), thorough attention will be dedicated to evaluating procedure-related complications, including arterial perforation, dissection (particularly involving the ICA), vasospasm, and embolization in new vascular territories. In particular, the risk of balloon rupture will be considered a specific complication associated with using iNedit catheters. It will be recorded and reported during the trial as a *post-hoc* analysis, even if it is expected to have no clinical relevance.

These complications will be systematically assessed by the local investigators, independently reviewed through imaging analysis by the external core lab, and adjudicated by an independent Clinical Events Committee (CEC) to ensure objective evaluation and accuracy.

Special attention will be given to outcomes related to the navigability of the devices as the balloon catheter has been specifically developed to improve the navigability compared to currently available balloon guide catheters. Previous studies of preliminary experiences with this device have reported high scores in terms of navigability (11).

In addition, we expect a lower incidence of vasospasm, as balloon inflation occurs at the petrous segment of the carotid artery, where the periosteal layer provides stability by attaching to both the vessel and the surrounding bone. This contrasts with the cervical ICA, which is more prone to collapse due to being surrounded by the neck's soft tissues (19).

Integrating distal access, flow reversal, and flow arrest in mechanical thrombectomy potentially enhances clot retrieval efficiency, reduces embolization risk, and improves procedural safety. DACs allow closer proximity to the thrombus, providing stable support for thrombectomy devices, improving clot retrieval, and facilitating direct aspiration. Flow reversal helps prevent clot fragmentation and distal migration during retrieval, while flow arrest enables safer retrieval of large thrombi and enhances overall procedural control.

A potential limitation of the strategy proposed by the current study is that the distal aspiration balloon catheter has an inner diameter of 0.058”, which refers to the width of the hollow tube that runs through the center of the device. This may not be considered large enough to perform aspiration in certain cases with large clots, such as in the carotid T, according to some operators. However, this inner dimension may be advantageous for aspiration in distal vessels (20). A subgroup analysis comparing outcomes in M2 occlusions vs. the carotid T and M1 segments could support the future use of this catheter specifically for M2 occlusions, especially by inflating the distal balloon to achieve more effective flow arrest.

The main objective of this study is to demonstrate the feasibility and safety of the combined use of the three iVascular devices. The results of this study should be interpreted with caution due to its single-arm design, which may limit the ability to determine whether an alternative method would have yielded superior outcomes. However, a multicenter international study design has been implemented to reduce center-specific biases and enhance the generalizability of the findings. Furthermore, a secondary propensity score matching analysis will account for potential confounding factors by comparing similar patients treated with alternative methods.

The results of the SEMTiC studies, expected to be available in 2025, will answer whether combining flow arrest, flow reversal, and distal access (SEMTiC strategy) is an effective and safe strategy for performing mechanical thrombectomy.
